#### Prohibited therapies

3.5.3

Any therapies that might alleviate cervicobrachial pain beyond usual care will be prohibited during study participation, including dehydrating agents, neurotrophic drugs, skeletal muscle relaxants, Chinese herbal medicine, acupuncture, cupping, physical therapy and exercise therapy. Participants who consider pain reduction to be insufficient may seek alternative therapeutic options, but will be withdrawn from the trial.

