The EQ-5D-5L is a readily available generic health status instrument which has shown reliability and validity on musculoskeletal problems (57). It consists of a visual analog scale (EQ-VAS) from 0 to 100 and a five-item descriptive system, with each item having five response levels of severity (58). The digits which participants mark on the EQ-VAS represent their perceived overall health on the day of being interviewed. The five ticked response levels in the descriptive system can be derived into a 0-to-1 index value employing a country-specific ‘value set’ to express a health state profile. Higher EQ-VAS and EQ-5D-5L index values both reveal a better quality of life. In our trial, a Chinese version of EQ-5D-5L obtained from the official website (59) and the China-specific ‘value set’ (60) will be applied. However, the EQ-5D-5L index values will be converted into quality-adjusted life years (QALYs) to inform economic evaluations of interventions.

The SDS (61) and SAS (62) are self-administered instruments for rating depression and anxiety severity based on the frequency of affective and somatic symptoms during the preceding week. Each contains 20 questions scored from 1 to 4 on a 4-point Likert scale based on the perceived frequency, all yielding a raw summation range of 20 to 80. The raw summations will be converted into index scores by multiplying them by 1.25. The index scores can categorize depression as nil (25–49), mild (50–59), moderate (60–69), or severe (70+), and anxiety as nil (25–44), mild (45–59), moderate (60–74), or severe (75+) (63). The Chinese versions (64, 65) which have been demonstrated to have extensive reliability and validity among the Chinese population (66, 67) will be administered in our trial.

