The WPAI: CR is a revised questionnaire constructed by specifying “cervical radiculopathy (CR)” in the Work Productivity and Activity Impairment Questionnaire: Specific Health Problem V2.0 (WPAI: SHP). The WPAI: SHP is a six-item patient-reported instrument created for capturing the amount of work time missed, on-the-job effectiveness reduced, and daily activity impairment during the previous 7 days due to a specific health problem (68, 69). The official user guide encourages adapting the WPAI: SHP to any specific health problem by inserting the name of the disease or condition of interest wherever the word ‘PROBLEM’ appears in the WPAI: SHP template (70). In our trial, CR-related work productivity loss will be quantified based on the revised WPAI: CR through per cent work time missed, impairment while working, overall work impairment and activity impairment (71). Greater values indicate less productivity.

Additional secondary outcome measures will include adverse event rate (AER), adverse reaction rate (ARR) and intervention cost. Any undesirable experiences from which participants suffer post-enrolment will be identified as adverse events (AE), and those associated with the intervention will be defined as adverse reactions, while those that result in hospitalization, loss of ability to work, disability, congenital deformity, or death will be listed as serious adverse events (SAE). Any AE during the study will be recorded. The cost of intervention will be based on a societal perspective, and composed of direct medical costs (DMC), direct non-medical costs (DnMC) and indirect costs (IDC) (72). The composition of direct costs are detailed in Table 2, and the composed item cost will be obtained by resource volumes multiplied by their respective unit costs (73). The IDC will be estimated using the human capital approach, which is the product of labor loss time and the unit labor value (72–74). In this trial, labor loss time will encompass the work time missed by both participants and their accompanying family members. The unit labor value will be based on the per capita GDP of Guangzhou in 2024 (73). DMC, DnMC, and the accompanying family’s missed work time will be collected at every visit. The participants’ missed work time will be collected via the WPAI: CR.

**Table 2 tab2:** Composition and determination of direct costs.

Cost composition	Basis for unit cost calculation

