DMC resulting from registration, magnetic resonance imaging, NSAIDs and opiates, cervical collars, and AMTs	price summary list of basic medical services in Guangzhou
DMC resulting from adverse reactions	actual costs incurred during the trial
DnMC resulting from round-trip travel, meal and lodging	actual costs incurred during the trial

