The TMG assumes responsibility for day-to-day trial operations. It will consist of a project manager, a registered research physician, a registered therapist, a trial coordinator, two research assistants and a data manager. All members will attend a pre-trial training workshop to familiarize themselves with the trial implementation process, and to ensure adherence to the study protocol and standard operating procedures. The trial coordinator is to formulate follow-up programs based on the study protocol. They will keep in touch with participants to facilitate their attendance at scheduled follow-ups, but also to assist in promptly detecting any AE. The research assistants will collect and record data on paper case report forms (CRF), including participants’ socio-demographics (age, sex, education level, employment status, health insurance, etc.), medical history (comorbidities, concomitant medications, details related to the cervicobrachial pain episode, etc.) and physical examination at baseline (dominant hand, abnormal deep tendon reflexes, radiculopathy level shown on magnetic resonance imaging, etc.) and discharge (abnormal deep tendon reflexes), secondary outcomes, treatment information, and adverse event details. Data may be collected within 1 day after the scheduled time. Unless they explicitly refuse, research assistants will follow up with any withdrawn participants to acquire data until the trial end. Additionally, they will track any AE from reporting until resolution. The data manager will regularly monitor data quality, working with research assistants to recover missing data and clarify ambiguous data to ensure all reported data are accurate, complete, legible and verifiable from source documents. Research assistants will double-enter the data from the paper CRF after monitoring into an Epidata-based electronic data capture system. Any discrepancies from double entry will be verified against the paper CRF. The data manager will lock the electronic data capture after all data have been cleaned; researchers will be unable to modify the data. The TMG will meet weekly to review study progress during the trial. The project manager will meet with the TSC biweekly to align on key decisions.

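### Table 2 has no row for the therapy that participants switch to, so the cost outcome is not the societal cost it is said to be, although switchers' health and work data still count in their arm

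*Protocol article*

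**What the plan says.** On costs, section 3.6.2 states: "The cost of intervention will be based on a societal perspective". It then says: "The composition of direct costs are detailed in Table 2". Table 2 has three rows:

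- "DMC resulting from registration, magnetic resonance imaging, NSAIDs and opiates, cervical collars, and AMTs"
- "DMC resulting from adverse reactions"
- "DnMC resulting from round-trip travel, meal and lodging"

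Indirect costs are added separately, from work time missed by participants and by accompanying family.

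On switching, section 3.5.3 states: "Participants who consider pain reduction to be insufficient may seek alternative therapeutic options, but will be withdrawn from the trial". On data after withdrawal, section 3.8 states: "Unless they explicitly refuse, research assistants will follow up with any withdrawn participants to acquire data until the trial end".

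On effects, section 3.6.2 says that "the EQ-5D-5L index values will be converted into quality-adjusted life years (QALYs) to inform economic evaluations of interventions". Section 3.7.2 analyses secondary outcomes by intention to treat and imputes missing data. It reports intervention costs descriptively by group.

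**The concern.** A cost comparison and its matching health effects should cover the same care. Here they do not. The plan foresees that some participants will leave trial care for something else, keeps them in their randomized arm and goes on measuring their health. Its cost list, however, stops at trial care, adverse reactions and travel. Any improvement that a followed switcher gets from the other therapy is credited to the randomized arm, while the direct medical cost of that therapy appears nowhere. That is narrower than a societal perspective.

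The pilot is meant to prepare a definitive trial of clinical efficacy and cost-effectiveness (sections 2 and 6). The introduction suggests that AMT may lower health care costs, and less need for other care is one way this could happen. A cost form without the item cannot show whether that is so. It also leaves untested whether off-protocol care after withdrawal can be collected at all, although completion of cost measures is one of the pilot's feasibility outcomes (section 3.6.1).

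**Working it through.** The plan states no figure on this point, so there is none to reproduce. The check is a reading of the sections together, followed by illustrative arithmetic.

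**What happens to a switcher's data**

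| Item | Counted in the randomized arm? | Source |
|---|---|---|
| EQ-5D-5L and QALYs, pain, function | Yes, if the participant does not refuse follow-up; otherwise imputed | 3.6.2, 3.7.2, 3.8 |
| Participant's and family's missed work | Yes, if followed | 3.6.2 |
| NSAIDs and opiates | Yes, they have a row | Table 2 |
| Travel, meals, lodging | They have a row; whether trips for non-trial care count is not said | Table 2 |
| Direct medical cost of any other therapy | No row | Table 2 |

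Section 3.5.3 itself names therapies that fall in the last line: muscle relaxants, neurotrophic drugs, herbal medicine, acupuncture, cupping, physical therapy and exercise therapy.

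**Inputs**

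- n = 24 per arm (section 3.1: 48 participants, 24 of them in the experimental group).
- s_C and s_E: followed switchers in the control and AMT arms. Not given, so assumed.
- c: mean direct medical cost of non-listed therapy per switcher. Not given, so left as a symbol.

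**Formulas**

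- Understatement of an arm's mean cost = (s/24) × c.
- Error in the AMT-minus-control cost difference (reported minus true) = (s_C × c_C − s_E × c_E)/24. With equal cost per switcher this is c × (s_C − s_E)/24.

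**Understatement of one arm's mean**

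- 1 switcher: 1/24 = 0.042c
- 3 switchers: 3/24 = 0.125c
- 5 switchers: 5/24 = 0.208c
- 7 switchers: 7/24 = 0.292c

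For scale, the 80% retention target applied to one arm allows 0.20 × 24 = 4.8 drop-outs. If every one were a switcher, the understatement would be 4.8/24 = 0.20c. The 70% infeasibility limit allows 0.30 × 24 = 7.2, or 0.30c.

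**Error in the difference, equal cost per switcher**

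| Control switchers | AMT switchers | Error in AMT minus control |
|---|---|---|
| 3 | 1 | (3 − 1)/24 = +0.083c |
| 5 | 0 | (5 − 0)/24 = +0.208c |
| 5 | 5 | 0 |
| 0 | 5 | (0 − 5)/24 = −0.208c |

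Equal numbers do not remove the error if costs differ. With 3 switchers in each arm at 2c in control and c in AMT, it is (3 × 2c − 3 × c)/24 = +0.125c.

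**The case against.** **No decision in the pilot rests on cost.** The outcome is called intervention cost and is only described by group. There is no cost-effectiveness ratio, cost test or cost-based progression rule, and the success criteria in section 4 are enrolment, adherence and retention. This stands, and it limits the consequence. It does not make the list fit the label: a societal perspective, family work time and QALYs go beyond the cost of supplying the intervention.

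**An article condenses a fuller protocol.** This does not answer the point. Table 2 is presented as the composition of direct costs and has no line for other care. It is a stated rule, not an omitted detail.

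**Part of the information is already collected.** Concomitant medication is recorded during the trial (Figure 1), and treatment information goes on the case report form (section 3.8). This stands and makes the fix easier. But recording is not costing, and acupuncture or physical therapy is not medication.

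**Stronger readings that a reader might infer.**

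- That usual care is made to look too cheap, because dissatisfied participants would more often be in the arm without AMT. That is plausible, but the protocol says nothing about switching by arm, and the error changes sign if AMT participants switch more.
- That an expensive rescue such as surgery could overturn a cost conclusion. Section 3.5.3 does not mention surgery, section 3.2 excludes people planning it during the study, no prices are given, and no cost conclusion is planned.
- That every switcher's health gain is counted. It is observed only for those who do not refuse follow-up; for the others the values are imputed.

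**Conclusion.** The point holds as a mismatch between the stated perspective and the fixed cost list. Following the plan as written, the direct medical cost of non-listed therapy is left out for participants whose later health and work data remain in the analysis. Each arm's mean cost is too low by (switchers/24) × cost per switcher: about 0.04c for one switcher and about 0.2c at the retention target if every drop-out is a switcher. The between-arm difference is right only if the total omitted cost is the same in both arms.

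These figures assume 24 analysed per arm and a common mean cost c. Neither the direction nor the size in money can be derived from the protocol. What is affected is the descriptive cost comparison, together with the cost form and cost estimates taken into the definitive trial. The feasibility criteria are not affected.

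**What to change.** Add one row to Table 2: *DMC resulting from non-trial or prohibited therapy for the neck condition up to the fifth-period visit, including after withdrawal; basis: actual costs incurred during the trial.* This is the basis Table 2 already uses for adverse reactions. Add one line to the case report form, and collect it in the follow-up of withdrawn participants that section 3.8 already provides. Report costs by arm with and without this row, and give the number of switchers per arm.

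Thirty-three of the 48 participants had been recruited by 31 July 2025. For those who have already finished, take what the concomitant-medication records hold and ask for the rest by recall, or flag the item as not collected.

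If the row is not added, describe the outcome as the cost of trial-provided care instead of a societal cost, state the omission as a limitation, and put the item on the definitive trial's cost form.

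The cost is one table row and one form line. The downside is some recall-based or missing cost data, of uneven quality between earlier and later participants. No treatment or withdrawal rule has to change.

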### Statistical methods

3.7

#### Sample size

3.7.1

The primary objective of the pAMTLER is to determine the feasibility of a future definitive full-scale RCT based on recruitment rate, retention rate, and intervention acceptability. With pre-specified feasibility thresholds of ≥25% recruitment, ≥80% retention and ≥80% adherence, at least 48 eligible participants are required to have a 95% confidence interval with a maximum width of 20% (75). This sample size, in a resource-limited setting, is considered adequate to provide a reasonable estimate of outcome variability across the four strata (12 participants per stratum), defined by sex and baseline cervicobrachial pain level (75).

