### Study design

3.1

The **p**ilot study on **A**ngled **M**anual **T**raction and usua**L** car**E** for cervical **R**adiculopathy (pAMTLER) will be an open-label RCT with two parallel groups and blind evaluation. In this five-period (7 days per period) trial with a total of 15 visits, 48 eligible participants with CR will be enrolled. All enrolled participants will receive usual care for four periods. The 24 participants randomly assigned to the experimental group will also receive 14 sessions of AMT. The baseline will be defined as the pre-treatment assessment during the initial visit in the first period after randomization. Participants will be scheduled to complete the outcome assessments prior to treatment during the initial visit in each period. Figure 1 illustrates the study design. The pAMTLER will be conducted at the Guangdong Provincial Hospital of Chinese Medicine (GPHCM), Guangzhou, China, with approval from the Ethics Committee at GPHCM (approval number: BF2024-156-01). The study protocol was registered with ChiCTR2400087289, and is reported according to the Standard Protocol Items: Recommendations for Interventional Trials (SPIRIT) (31) (Appendix S2). Figure 2 overviews the participant flow and details the assessed content at each scheduled visit (Appendix S3).

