### Recruitment

3.3

Potential participants will be recruited by clinicians at GPHCM’s orthopedic outpatient clinics, as well as through advertisements issued via GPHCM’s official accounts, social media platforms including TikTok and WeChat (Tencent), and newspapers. Interested individuals will be encouraged to contact the researcher (a registered research physician responsible for usual care), using the private telephone line listed on the recruitment flyers in clinic or the advertisements. The research physician will be independent of the outcome assessment and random allocation process. He will identify candidates who fulfill the CR diagnostic criteria among the approached individuals, and invite them to participate in the pAMTLER after informing them of the study’s purpose, procedure, as well as participation benefits and potential risks. Willing candidates will be further assessed for eligibility according to the inclusion and exclusion criteria after voluntarily signing written informed consent forms. Those eligible to participate in the post-evaluation will then be consecutively enrolled and randomized. The randomized individuals can withdraw participation consent at any time during the trial without prejudice. Details related to screening, enrolment, withdrawal, and reasons for non-participation will be documented in a prearranged register.

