#### Primary outcome measurements

3.6.1

Measures that indicate the feasibility of the future full-scale RCT will serve as primary outcomes. They will be:

enrolment rate: the proportion of recruited participants who are randomized.weekly enrolment rate: the number of participants to be randomized per week over the trial recruitment duration.drop-out rates: the proportion of participants who either withdraw or are lost to follow-up at the initial visits of the 2nd, 3rd, 4th, or 5th periods.retention rates: the proportion of non-dropout participants (i.e., those completing all follow-up measurements) at the initial visits of the 2nd, 3rd, 4th, and 5th periods.adherence rates: the proportion of participants completing the planned number of treatment sessions after randomization (the proportion completing 14 sessions of AMT in the experimental group and attending 4 usual care prescriptions in the control group, respectively).completion rates of efficacy-related outcome measures: the proportion of completed efficacy outcome measures relative to those intended for assessment at the initial visit per period.completion rates of cost-related outcome measures: the proportion of completed cost outcome measures relative to those intended for assessment at every visit during the trial.

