#### Data analysis

3.7.2

Data will be statistically analyzed using PASW Statistics 18.0, STATA 14.0 and R 4.3.0. Continuous variables will be summarized as means with standard deviations or medians with interquartile ranges, whereas categorical variables will be presented as counts and percentages. The primary outcome will be outlined using descriptive statistics. Building on reported positive associations between colder temperatures, male sex, and more consultations for musculoskeletal pain (76), we will conduct subgroup analyses to explore how season and sex influence enrolment, retention, and adherence, thereby informing weather-adaptive management strategies for the future full RCT. Secondary outcome measures will be analyzed based on the intention-to-treat population approach. Any post-randomization participants who received at least one intervention session will be included in the full analysis set. Among these, those who completed at least 80% of the planned treatments without any significant protocol violations will be categorized into the per-protocol analysis set. Any post-randomization participants receiving at least one intervention session will be classified into the safety analysis set. Any missing data will primarily be handled using multiple imputation, with last observation carried forward applied for sensitivity analysis.

We will analyze both within- and between-group changes for each efficacy-related secondary outcome variable using a linear mixed-effects model to derive estimates of intervention effects.

Group allocation, time-point and the interaction between group allocation and time-point will act as fixed-effects, individuals as random effects, and baseline measurements as covariates. Given that this exploratory trial is not formally powered to assess effects, a recommended confidence interval of 75% will be employed to infer the size and direction of the calculated effect estimates (77). The 75% confidence interval will be compared with the MCIDs to preliminarily assess whether the difference between treatment groups holds potential for clinical significance (77). The remaining secondary outcome measures involving AER, ARR, and intervention costs, as well as baseline variables, will be presented descriptively by the groups.

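### At the 80% retention and adherence thresholds, 48 participants do not give a 95% confidence interval as narrow as 20 points: the width is about 23 points for all 48 and about 32 points for adherence within one arm

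*Protocol article*

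**What the plan says.** Section 3.7.1 (Sample size) of the protocol article bases the number on the precision of the feasibility rates. It begins "With pre-specified feasibility thresholds of ≥25% recruitment, ≥80% retention and ≥80% adherence" and concludes that "at least 48 eligible participants are required to have a 95% confidence interval with a maximum width of 20" per cent. It gives no interval method, dropout allowance or per-arm basis.

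The denominators are fixed elsewhere:

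- **Arm size.** Section 3.1 has "The 24 participants randomly assigned to the experimental group will also receive 14 sessions of AMT", with 48 in total.
- **Adherence.** Section 3.6.1 defines it by arm: "the proportion completing 14 sessions of AMT in the experimental group and attending 4 usual care prescriptions in the control group, respectively".
- **Enrolment.** Section 3.6.1 defines "enrolment rate: the proportion of recruited participants who are randomized", so the 48 are its numerator, not its denominator.

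Section 4 (Results) sets success at 80% or more for adherence and for retention, and says the trial may be infeasible if either is below 70%.

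Section 3.7.1 adds that the sample is "considered adequate to provide a reasonable estimate of outcome variability across the four strata (12 participants per stratum"), the strata being sex by baseline pain. Section 3.3 says "Those eligible to participate in the post-evaluation will then be consecutively enrolled and randomized".

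**The concern.** The precision sentence is the only quantitative justification offered for 48, and its inputs are printed beside it: 95% confidence, a 20-point width and the three thresholds. Those inputs do not lead to 48 at the 80% thresholds.

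This matters because of where the plan puts its cut-offs. A 20-point interval centred on 80% runs from 70% to 90%. A reader who trusts the sentence will conclude that an observed 80% just excludes the region where the trial may be infeasible. If the true interval is wider, an observed 80% does not exclude that region. The gap is largest for adherence to the 14-session traction schedule, which is measured in only 24 people.

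**Working it through.** **Inputs.** Confidence 95% (z = 1.96), full width w = 0.20, N = 48 and p = 0.25, 0.80, 0.80 (section 3.7.1). Arm size 24 (section 3.1). Adherence by arm, and enrolment among those recruited (section 3.6.1).

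**1. Attempt to reproduce 48.** For one proportion, n = 4z²p(1−p)/w².

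- At p = 0.80: 4 × 3.8416 × 0.16 / 0.04 = 61.5, so 62. Other methods give 60 (Wilson, Jeffreys), 62 (Agresti-Coull) and 70 (Clopper-Pearson). None gives 48.

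**2. Width that 48 gives at 80%.** Wald width = 2z√(p(1−p)/n).

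- 2 × 1.96 × √(0.16/48) = 0.226, or ±11.3 points.
- Wilson and Jeffreys give 22.2 points, Agresti-Coull 22.6 and Clopper-Pearson 24.2.
- The Wald width falls to 20 points only at an observed rate of about 85.4% or more (41/48: 19.97 points).

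**3. Width for adherence in one arm, n = 24, at 80%.**

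- 2 × 1.96 × √(0.16/24) = 0.320, or ±16.0 points. Other methods give 30.9 to 34.6 points.

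**4. Lower limit for an observed 80%, against the 70% cut-off.**

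| Basis | Wald lower limit | Wilson lower limit |
|---|---|---|
| As stated (±10 points) | 70.0% | – |
| All 48 | 80 − 11.3 = 68.7% | 66.7% |
| One arm, 24 | 80 − 16.0 = 64.0% | 60.4% |

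**5. Enrolment at 25%.** If 48 are randomized at exactly 25%, the denominator is 48/0.25 = 192. This is an assumption, because the document gives no screening total.

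- 2 × 1.96 × √(0.25 × 0.75/192) = 0.1225, about 12 points, which is within 20.

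**6. Other readings of the sentence.**

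- Width taken as half-width, worst case p = 0.5, per arm: 3.8416 × 0.25 / 0.04 = 24.01. Two arms give 48.02.
- Width taken as half-width at p = 0.80, all participants: 3.8416 × 0.16 / 0.04 = 15.4, so 16.
- 90% confidence, full width 20 points, p = 0.80: 43.3. Allowing 10% dropout, 43.3/0.9 = 48.1.

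**7. Strata.** 48/4 = 12 is the average. Allocation is stratified, which balances the arms within each stratum but does not fix stratum sizes. Entry is consecutive and no quota is stated. If all four strata were equally common, which is an assumption and the most favourable case, simulation of 48 entrants puts the smallest stratum at about 8.5 on average.

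**The case against.** The best defence is that the margin was mislabelled. A half-width of 20 points at p = 0.5 needs about 24 per arm, the design has 24 per arm, adherence is defined by arm, and the word maximum suits a worst-case proportion. That is a plausible origin for 48, and the source cited for it is not available here. It does not make the printed sentence true. The sentence says width, not half-width, and ties the figure to 25% and 80%, not 50%. If this was the intention, the plan is claiming ±20 points per arm and should say so. The 90%-with-dropout reading fails too, since the text says 95% and mentions no dropout.

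The defence is also right that the overall miss is modest, at 2.6 points of width. Success and infeasibility in section 4 are judged on the observed rates, not on interval limits, so no stated decision rule changes.

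A reader might infer further faults that the document does not support:

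- **That enrolment also misses 20 points.** This holds only if 48 is its denominator, and section 3.6.1 rules that out.
- **That the plan promises 12 people in every stratum, or stratum-specific variability estimates.** Twelve reads naturally as 48/4, and section 3.7.2 fits one model to all participants. Exact equality across strata is improbable, but nobody would promise it.
- **That no intervals are planned for the primary outcome.** Section 3.7.2 says "The primary outcome will be outlined using descriptive statistics". That does not exclude intervals around proportions, and such detail may sit in a fuller document.

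**Conclusion.** The precision statement in section 3.7.1 is not true as written for the 80% thresholds. The true width is 22.6 points for all 48 (Wald; 22.2 to 24.2 by other methods) and about 32 points for adherence in one arm. For an observed 80%, neither the overall nor the arm-level interval excludes the plan's own region below 70%, although the stated precision suggests that it just would.

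This rests on reading width as full width, on the printed thresholds and confidence level, and on retention being reported over all 48. If retention were reported by arm, the 32-point figure would apply to it too. If adherence were pooled against its definition, its width would still be 22.6 points. The enrolment result depends on the assumed 192.

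A reader might also infer that 48 is too few and must rise to 62. That does not follow. A pilot may accept wider intervals, and the fault lies in the stated precision, not in the choice of 48.

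**What to change.** Keep N = 48 and rewrite the precision sentence in section 3.7.1 to say what 48 gives: at 80%, about ±11 points for overall retention and about ±16 points for adherence in each arm of 24. For enrolment, state about 12 points of full width if about 192 people form the denominator, and label that as an assumption. If the basis was in fact ±20 points per arm at a worst-case 50%, say so explicitly.

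State that 95% Wilson intervals will be reported beside the feasibility rates, so that closeness to the 70% and 80% cut-offs is visible. Describe 12 per stratum as an expected average.

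The cost is wording only, with no extra participants and no change to the design. The one downside is that the stated precision becomes less favourable, slightly for retention and more clearly for adherence by arm.
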